### Interventions

Home care professionals in the intervention group will follow the ‘Stay Active at Home’ programme. The programme lasts for 9 months and consists of face-to-face meetings, practical assignments in-between the meetings and twenty weekly newsletters. The face-to-face meetings can be subdivided into a kick-off meeting (120 min), a series of (bi-)monthly team meetings (60 min each) which are spread over a period of 6 months, and a booster session (120 min) 3 months later (see Fig. 2 for an overview of the training programme). The kick-off meeting and booster session are the same for nursing teams and DSWs. Professionals from both disciplines, who are working in the same working area, are invited to the sessions to get to know each other. The team meetings are offered to nursing teams and DSWs separately, as these meetings are more focused on discipline-specific tasks. DSWs have fewer team meetings than nursing teams (three and five meetings, respectively), as they have a lower annual time-budget for training activities. During the programme, professionals receive background information about the benefits of Reablement. Furthermore, they learn skills to apply it in practice: (1) assessing capabilities of older adults; (2) implementing goal-setting and action planning; (3) increasing engagement of older adults in physical and daily activities; (4) motivating older adults by taking into account their phase of behavioural change [16, 17, 35, 36] and making use of Bandura’s self-efficacy theory [37, 38]; and (5) involving the social network of older adults. Professionals can practice these skills in a safe environment during the face-to-face meetings. Afterwards they are expected to apply the skills in practice as part of the practical assignments. Their experiences are discussed during the next meeting. Further details about the development and content of the programme are published elsewhere [18]. In addition, a brief movie about the ‘Stay Active at Home’ programme (in Dutch and English) can be found at: https://www.academischewerkplaatsouderenzorg.nl/research-programme/15521.

**Fig. 2 Fig2:**
[figure not shown]
Format and content of the ‘Stay Active at Home’ programme

Professionals in the control group receive no additional training.

#### Primary outcome measure

The aim of the ‘Stay Active at Home’ programme is to reduce sedentary behaviour in older adults and thereby increase their level of physical activity. The primary outcome sedentary behaviour at 12 months will be measured by means of a tri-axial wrist-worn accelerometer (ActiGraph GT9X Link, ActiGraph Inc., Pensacola, FL, USA). Accelerometers are a valid and reliable method, also in older adults, to measure sedentary time and physical activity by assessing the magnitude of the body’s acceleration in terms of ‘counts’ per unit time [39–43]. The ActiGraph will be placed on the non-dominant wrist and will be worn for seven consecutive days (24 h per day) at baseline and 12 months after baseline. As the accelerometer will also be worn during the night, information about sleep will also be obtained. Older adults are asked to keep a diary to register when they went to bed, when they got up and when they were napping during the day. Data will be collected at 30 Hz and will be aggregated to 60-s epochs for the analyses [44]. Older adults are required to have at least 1 valid day of 10 h of wake wear time to be included in the analyses. In additional analyses, older adults with four or more valid days will be selected. Waking time and wear time will be defined by an algorithm available in the ActiLife software version 6. Activity counts will be converted into average daily minutes of sedentary behaviour during waking time using a vector magnitude cut-point of < 1853 cpm [45]. In addition, mean wake time activity counts per minute will be compared between groups (secondary outcome).

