#### Effect evaluation

Descriptive statistics will be used to describe the study groups regarding their sociodemographic characteristics and baseline scores of the primary and secondary outcomes. The primary and secondary outcomes will be analysed according to the intention to treat principle, that is, all available data from all participants will be included in the analysis. Mixed (multilevel) linear regression will be applied with repeated outcome measures (baseline, post-test) nested in clients nested in nursing teams. ‘Nursing team’ is treated as random effect and outcome predictors are: intervention (yes/ no), time (baseline/ post-test), the intervention by time interaction, working area and its interaction with time, as well as the following covariates and their interactions with treatment and time: 1) older adults’ initial level of disability (measured by means of the GARS [50]); 2) client type (existing vs. new clients); 3) working areas. The design, with one team per working area per treatment condition, does not allow including a random team effect and working area by treatment interaction at the same time, because the team effect is completely confounded with the latter interaction. Team is here the unit of randomisation and therefore treated as random. However, to explore interaction of treatment with working area, an additional analysis will replace the random team effect with that interaction and three-way interaction area*treatment*time. If interaction is found, the treatment effect will be evaluated per working area. The software package SPSS for Windows, version 24.0., will be used for all statistical analyses. The level of statistical significance will be set at 0.05 (using two-tailed tests). If interaction effects for the three covariates (i.e. older adults’ initial level of disability; client type; and working area) are present subgroup analyses will be conducted with a significance level of 0.10. The subgroup analyses will have an exploratory purpose only in view of the risk of type I errors due to multiple testing and of type II errors due to reduced sample size.

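### The primary outcome is raw sedentary minutes with no adjustment for wake wear time, so a change in wear that differs between arms would pass for a change in sedentary behaviour

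*Protocol article*

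**What the plan says.** The section on the primary outcome measure defines the endpoint as follows, by means of a count cut-point: "Activity counts will be converted into average daily minutes of sedentary behaviour during waking time". The device "will be worn for seven consecutive days (24 h per day) at baseline and 12 months after baseline". Entry to the analysis is lenient: "Older adults are required to have at least 1 valid day of 10 h of wake wear time to be included in the analyses". On how wear is obtained it says: "Waking time and wear time will be defined by an algorithm available in the ActiLife software version 6". The only stated use of wear time is to decide which days are valid.

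Two further analyses are planned. One restricts the number of days: "In additional analyses, older adults with four or more valid days will be selected". The other compares mean counts per minute of waking time between groups, as a secondary outcome.

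The Effect evaluation subsection of Data analyses lists the model terms: intervention, time, their interaction, working area and its interaction with time, and three covariates with their interactions with treatment and time. The covariates are baseline disability on the GARS, then "2) client type (existing vs. new clients); 3) working areas". Wear time is not among them, and no proportion of wear time or standardised day is defined. The Sample size section sizes the trial in minutes per day.

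**The concern.** Only worn minutes can be scored as sedentary. Two people with the same habits get different totals if one wears the device for fewer waking hours, and the direction is fixed: less wear gives fewer sedentary minutes. If wear in the intervention arm fell more between baseline and 12 months than in the control arm, the result would look like benefit. If it fell more in the control arm, a real benefit would be hidden.

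Neither additional analysis settles this. Requiring four valid days sets how many days count, not how many hours each day holds. Counts per minute is normalised for wear, but it is secondary and measures activity intensity rather than sedentary time. Sedentary time is also the outcome of the cost-effectiveness analysis, so the same shift would enter the denominator of that ratio.

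**Working it through.** **Inputs from the protocol article**
- Mean 535.9 min/day, SD 145.7, expected difference 15%, power 80%, two-sided alpha 0.05 (Sample size).
- Sedentary share about 80% of awake time, or 8 to 12 h per day (Background).
- Valid-day floor of 10 h of wake wear (Primary outcome measure).

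**Assumptions, not in the document**
- A 30-min difference between arms in the change in mean wake wear.
- An alternative sedentary share of 60 to 65%.
- A between-person SD of wake wear of 60 to 120 min.
- The calculation concerns minutes that the algorithm recognises as not worn.

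**1. The plan's own figures.** The planned difference is 0.15 × 535.9 = 80.4 min. The effect size is 80.4 / 145.7 = 0.55, as stated. The normal approximation gives 52 per group and the t-test 53, against the stated 54. Drop-out gives 108 / 0.7 = 154.3, against the stated 154. The sizing metric is therefore raw minutes, and the planned effect to compare with is 80.4 min.

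**2. When wear biases the estimate.** Let *p* be the sedentary share and *W* the wake wear in minutes, so that recorded sedentary time is *p* × *W*. If behaviour does not change and *p* is the same in both arms, the intervention-by-time contrast is

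*p* × [(change in *W*, intervention) − (change in *W*, control)].

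A stable difference in wear between arms gives zero, and so does a change shared by both arms. Only a differential change remains.

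**3. Size of the shift**

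| Sedentary share | Differential in wake wear | Shift | Share of 80.4 min |
|---|---|---|---|
| 80% (protocol) | 30 min | 24 min | 30% |
| 65% (assumed) | 30 min | 19.5 min | 24% |
| 60% (assumed) | 30 min | 18 min | 22% |

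To imitate the whole planned effect, the differential would have to be 80.4 / 0.80 = about 100 min at the protocol's share, or 80.4 / 0.60 = 134 min at 60%.

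**4. Noise.** With the assumed wear SDs, the part of the outcome variance linked to wear runs from (0.60 × 60)² / 145.7² = 0.06 to (0.65 × 120)² / 145.7² = 0.29.

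**5. What normalising does.** If sedentary time is divided by wake wear, *W* cancels and the shift in step 3 becomes zero at unchanged behaviour. A new sample size cannot be computed, because the document gives no SD for the normalised outcome.

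**The case against.** The strongest reply is that minutes per waking day is a proper outcome and that much of the variation in wake wear belongs to it. The device is worn around the clock, with a diary of bed, rising and nap times, so with good compliance wake wear is close to waking time. The Background figures imply 8 / 0.80 = 10 h to 12 / 0.80 = 15 h awake, so a 10 h day may be a complete waking day. This stands. A reader might set 10 h of wear (480 min at 80%) against 15 h (720 min) and call the 240-min gap artefact; the document does not support that, since the gap may be real waking time.

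Three other strong readings also go too far:
- **Any drift in wear between baseline and 12 months biases the result.** It does not. A drift common to both arms is absorbed by the time term.
- **Differential wear is to be expected because clients know their arm.** The document does not state clients' blinding status. Both arms get the same device and wear instruction, and one research team collects the data under one protocol.
- **Wear noise leaves the trial underpowered.** The SD of 145.7 is itself in minutes per day and comes from the same cited source as the cut-point. It may already contain this variation, so the 6 to 29% is at most a possible gain in precision.

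It is also fair that the plan is not silent on wear: the 10 h floor, the four-day analysis and counts per minute are partial safeguards. None of them, however, shows whether a difference in sedentary minutes comes from wear. Detail on accelerometer processing may sit in a fuller document, but the outcome metric and the list of predictors are fixed here.

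**Conclusion.** The point holds in a limited form. Neither the primary outcome nor its model accounts for wake wear time, so the planned analyses cannot separate less sitting from less wear if wear changes differently between arms. An assumed 30-min differential would move the estimate by 24 min at the protocol's 80% share (30% of the planned effect), or by 18 to 20 min at an assumed 60 to 65% (22 to 24%). Whether any differential will occur is unknown, so this is an exposure to bias and not a demonstrated bias.

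A reader might infer that the minutes outcome is invalid, or that the primary model should be replaced by one adjusted for wear. The document does not support that. Waking time is part of the stated outcome, the trial is sized in minutes, and wake wear at 12 months is measured after randomisation. If the programme alters napping or time in bed, adjustment could remove part of a real effect.

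**What to change.** Keep minutes per day as the primary and sizing metric, and prespecify the following before outcomes are compared by arm:

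1. Fit the same mixed model to sedentary time as a percentage of wake wear time on valid days. Minutes standardised to a fixed waking day would serve as well and can be set directly against the 80.4 min.
2. Report mean wake wear time on valid days by arm and time point.
3. State that a difference in minutes will be read as a change in sedentary behaviour only if the two analyses agree, and define agreement in advance, for example the same direction and a compatible size.

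The cost is one extra analysis and one table. No new data are needed, because the ActiLife software already derives wear time. The downside is that the normalised result answers a slightly different question, since wake wear is itself measured after randomisation. For that reason it stands beside the minutes analysis and does not replace it.

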#### Secondary outcome measures

The LASA Sedentary Behaviour questionnaire [46] will be used to assess self-reported sedentary behaviour. The questionnaire consists of 10 items about sedentary activities such as watching television. Older adults will report the time that they generally spent on each sedentary activity per day. The items must be completed for one weekday and one weekend day. Total self-reported sedentary time (in minutes) for an average day will be calculated as ((total sedentary time on weekdays * 5) + (total sedentary time on weekend days * 2))/7. A previous study has shown that self-reported sedentary time measured by the LASA Sedentary Behaviour questionnaire can reliably rank sedentary time in in older persons and was moderately associated with accelerometer-derived sedentary time [46].

Physical functioning will be measured by the Short Physical Performance Battery (SPPB, [47]). The SPPB is based on three objective tests of physical function: 3-m walking speed, repeated chair stands (five times), and standing balance in progressively more-challenging positions (i.e. feet in side-by-side, semi-tandem, and full-tandem positions). Each test is scored 0 to 4 by previously determined criteria [48]. Scores from the three tests will be summed into a composite score ranging from 0 to 12, with higher scores reflecting better physical functioning. The SPPB has excellent reliability [49] and is highly sensitive to important changes such as self-reported decline in ability to walk a block or to climb one flight of stairs. Decreased SPPB is a strong predictor of nursing home admission, disability in self-care tasks, and mobility in older adults [48, 49].

The Groningen Activity Restriction Scale (GARS, [50]) will be used to collect data about daily functioning. The GARS consists of two subscales and assesses disability in the domains of activities of daily living (ADL, 11 items, such as dressing or getting around in the house) and instrumental activities of daily living (IADL, 7 items, such as preparing breakfast or doing household activities) [50]. For each item, four hierarchical answer options are available ranging from *‘Yes, I can do it fully independently without any difficulty’* to *‘No, I cannot do it fully independently. I can only do it with someone’s help’*. The scores for the total scale range from 18 to 72 with higher scores indicating more disability [50]. The GARS is a reliable and valid measure for assessing disability in the domains of ADL and IADL in older adults [50].

The Patient Health Questionnaire-9 (PHQ-9, [47]) will be used to assess psychological functioning. The PHQ-9 consists of nine items which measure the presence of depressive symptoms according to the Diagnostic and Statistical Manual of Mental Disorders, 4th Edition (DSM-IV). Older adults will score how often each of the symptoms (such as ‘little interest or pleasure in doing things’ or ‘feeling tired or having little energy’) was present during the last two weeks (0 = not at all; 1 = several days; 2 = more than half of the days; 3 = nearly every day). The summary score ranges from 0 to 27, with higher scores reflecting more severe symptoms of depression. The PHQ-9 has been shown to be a valid and reliable instrument to measure depression in community-dwelling older adults [51].

Finally, the frequency of falls will be assessed by the question: *‘How often did you fall during the past 6 months’* [52]. This question is included to monitor a potential negative outcome of physical activity, despite research showed that stimulating older adults to be more active does not necessarily lead to an increase in fall incidents [53].

### Economic evaluation

The economic evaluation will be conducted according to the Dutch guidelines of economic evaluations in health care [54, 55], which were developed in agreement with international standards. A combination of cost-effectiveness analysis (CEA) and cost-utility analysis (CUA) will be performed from a societal perspective, which implies that all relevant outcomes will be taken into account (i.e. intervention costs, health care costs, patient and family costs) [54, 55]. Self-reported data will be collected together with the data for the effect evaluation by the research team at baseline and 6 and/or 12 months after baseline. In addition, data from client records will be extracted at the end of the study. An overview of all collected data is provided in Table 2. The time horizon will be the same period as the follow-up period of the effect evaluation (i.e. 12 months).

**Table 2 Tab2:** Overview of economic evaluation data collection

Outcomes	Measures	No. of items	Range^a^	Time points		
				*Baseline (T0)*	*Follow-up 1: 6 months after baseline (T1)*	*Follow-up 2: 12 months after baseline (T2)*
Clinical outcomes						
*Sedentary behaviour*	ActiGraph GT9X Link	N/A	N/A	X		X
*Health-related quality of life*	QALYs (based on EuroQol-5D-5 L [56, 57]	5	0–1	X	X	X
Health care utilisation and costs						
*Health care utilisation*	Self-developed questionnaire based on iMTA Medical Consumption Questionnaire [61].	9	N/A	X	X	X
	Client records	N/A	N/A	Continuous registration		

^a^underlined scores indicate the most favourable scores; *N/A* not applicable

#### Clinical outcomes

The primary outcome measure for the CEA will be sedentary time. The primary outcome measure for the CUA will be generic quality adjusted life years (QALYs), measured by means of the standard newest Dutch version of the EuroQol-5D-5 L. (EQ-5D-5 L, [56, 57]). The EQ-5D-5 L consists of five dimensions of health-related quality of life, namely mobility, self-care, daily activities, pain/discomfort and depression/anxiety. Each dimension can be rated at five levels: ranging from ‘no problems’ to ‘major problems’ [58, 59]. The five dimensions can be summed into a health state. Utility values can be calculated for these health states, using preferences elicited from a general population, the so-called algorithm [60]. The utilities at the three time points (baseline and 6 and 12 months after baseline) will be used to calculate QALYs by means of the area under the curve method. In addition, the EQ visual analogue scale will be used to assess current health status [58, 59].

#### Health care utilisation and costs

Volumes of health care utilisation will be measured using a self-developed questionnaire (9 items), which is based on the iMTA Medical Consumption Questionnaire [61]. Additionally, data from client records will be extracted at the end of the study. Overall, the following health care and patient and family costs will be taken into account: 1) primary care (i.e. general practitioner, physiotherapy, day care; 2) hospital care, (i.e. acute care, outpatient medical services and hospital admission; 3) long-term care (i.e. rehabilitation clinic, nursing home and retirement home); 4) home care (i.e. domestic services, personal care, and nursing care); and 5) informal care. Intervention costs will be based on the time health care professionals spent on ‘Stay Active at Home’ training activities. The valuation of health care costs and patient and family costs will be based on the updated Dutch manual for cost analysis in health care research [55]. This manual recommends using standardised cost prices. Cost prices will be expressed in 2017 euros. If necessary, existing cost-prices will be updated to 2017 using the consumer price index.

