This study has several strengths. First, the ‘Stay Active at Home’ programme was developed based on international evidence and in close collaboration with Dutch and foreign stakeholders [18]. Second, prior to the present study an exploratory trial was conducted (ClinicalTrials.gov: NCT02904889 (Smeets RGM, Kempen GIJM, Hansen WAG, Zijlstra GAR, van Rossum E, de Man-van Ginkel JM, et al. Experiences of home care professionals with the Stay Active at Home programme targeting reablement of community-living older adults. A qualitative study, submitted for publication)). The aims of this exploratory trial were to obtain experiences with the ‘Stay Active at Home’ programme and to test the study design. During the exploratory trial, challenges were identified which led towards some adaptations regarding the programme and the study design. For example, the exploratory trial showed that home care professionals did not identify with the interventionists, which is essential requirement for successful behavioural change according to behaviour change theory [72, 73]. Therefore, professionals who have already followed the ‘Stay Active at Home’ programme will be used as role models during the upcoming training sessions to share their experiences with their colleagues. The recruitment procedure was also adapted. In the exploratory trial, the participating nursing teams were asked to recruit older adults, resulting in a low response rate as nurses felt not responsible for the recruitment. In the proposed cluster randomised controlled trial, older adults will receive a short informational letter and flyer about the study as an announcement for a subsequent telephone call to assess whether they are potentially interested in participating in this study. Written informed consent will be obtained by the research team during the first home visit. Third, a strong aspect of the current study is that a combination of effect, economic and process evaluations will be conducted. Randomised controlled trials in the field of Reablement combining these different evaluations are scarce, yet important to obtain a complete picture. However, some limitations of this study must be acknowledged. First, it is not feasible in this study to objectively measure whether a behavioural change in home care professionals has taken place, as it is not possible to make use of (video) observations in the home care setting. Therefore, we rely on self-reported behaviour by home care professionals, which can result in biases due to social desirability and unaware/unskilled behaviour. Second, for this study, a follow-up period of 12 months has been chosen. This period may be too short to show effects, as home care professionals must first change their own behaviour before we can expect a behavioural change in older adults or changes in the consequent cost-effective outcomes with regard to their health and wellbeing. However, a longer follow-up is not possible due to practical and financial reasons.

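### The intervention-cost rule names professionals' training time but not the trainers' time or newsletter production, which sits badly with the declared societal perspective

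*Protocol article*

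**What the plan says.** In the protocol article, the section Economic evaluation adopts a societal perspective, "which implies that all relevant outcomes will be taken into account (i.e. intervention costs, health care costs, patient and family costs"). The section Health care utilisation and costs lists five groups of health care and family costs in some detail. For the programme itself it has one sentence: "Intervention costs will be based on the time health care professionals spent on" the training activities. It ties the Dutch costing manual to health care costs and to patient and family costs, and names no valuation source for intervention costs.

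The section Interventions describes a nine-month programme that "consists of face-to-face meetings, practical assignments in-between the meetings and twenty weekly newsletters". The meetings are "a kick-off meeting (120 min), a series of (bi-)monthly team meetings (60 min each") and "a booster session (120 min) 3 months later". Also, "DSWs have fewer team meetings than nursing teams (three and five meetings, respectively"). Professionals in the control group get no additional training.

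The section Process evaluation and Table 3 list interventionists as other stakeholders, separate from home care professionals. The Discussion also separates the two groups when it reports that professionals in the exploratory trial did not identify with the interventionists.

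**The concern.** Under a societal perspective, the cost of an intervention is the cost of the resources used to deliver it. Here these include the people who run the sessions and the production of the newsletters, and the cost sentence names neither. It is a stated rule, so an analyst could follow it to the letter and leave these items out.

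The error would have a known direction. Only the intervention arm uses delivery resources, so any omitted positive cost reduces the difference in mean costs, which is the numerator of the incremental cost-effectiveness ratio (ICER). The bootstrap cloud moves down, and at every ceiling ratio the acceptability curve moves up or stays where it is.

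No listed data source would obviously fill the gap. Table 2 has no row for programme resources. The dose entry in Table 3 for professionals records how many attend, complete assignments and read newsletters, not trainer hours. The project logbook covers performance against protocol, adaptations, reach, and facilitators and barriers.

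**Working it through.** The documents give no intervention cost, trainer hours, hourly price or ICER, so there is no stated figure to reproduce. The check sets the cost rule against the programme's components and then gives a scale.

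**Step 1: what the stated basis can cover.**

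| Resource | Within professionals' time on training activities? |
|---|---|
| Nurses and domestic support workers (DSWs) attending meetings | Yes |
| Practical assignments, reading newsletters | Can be; Table 3 registers them with attendance as professionals' uptake |
| Role models in the sessions | Can be; they are professionals who already followed the programme and "will be used as role models during the upcoming training sessions" |
| Interventionists running the sessions | Not named; listed as a separate group |
| Producing the newsletters and materials | Not named |

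The gap is therefore the last two rows.

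**Step 2: contact time from the schedule in the section Interventions.**

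- Nurse: 120 + 5 × 60 + 120 = 540 min = 9 h.
- DSW: 120 + 3 × 60 + 120 = 420 min = 7 h.
- Trainer, per working area: 120 (joint kick-off) + 5 × 60 (nursing) + 3 × 60 (DSW) + 120 (joint booster) = 720 min = 12 h. This assumes separate nursing and DSW team meetings in each area.
- Five areas with one intervention team each: 5 × 12 = 60 h per trainer.

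**Step 3: scale per trial client.** The section Sample size plans 130 clients per arm, so 130 / 5 = 26 per team. The following inputs are assumptions: 1 to 2 trainers per meeting, preparation of 0 to 100% of contact time, EUR 30 to 75 per hour, and 10 to 15 nurses and 5 to 15 DSWs trained per area.

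- Trainer hours per area: 12 × 1 × 1 = 12 h to 12 × 2 × 2 = 48 h.
- Per trial client: 12 / 26 = 0.46 h to 48 / 26 = 1.85 h.
- Cost per trial client: 12 × 30 / 26 = EUR 14 to 48 × 75 / 26 = EUR 138.
- Professionals' meeting time per area: 10 × 9 + 5 × 7 = 125 h to 15 × 9 + 15 × 7 = 240 h.
- Trainer time relative to it: 12 / 240 = 5% to 48 / 125 = 38%.

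**Step 4: how far this scale moves.** The upper percentage pairs the most trainer time with the fewest trainees, and counts meetings only. If each professional also spent an assumed 5 h on assignments and newsletters, counted time becomes 125 + 15 × 5 = 200 h to 240 + 30 × 5 = 390 h. The range then falls to 12 / 390 = 3% to 48 / 200 = 24%.

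The cost per client falls in proportion to the number of clients over whom it is spread. If the teams served twice as many clients as are enrolled (an assumption), EUR 14 to 138 becomes EUR 7 to 69.

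Newsletter production cannot be costed from the documents. Nor can the euro amounts be turned into an ICER shift, because the documents give no expected QALY gain.

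**The case against.** The strongest reply is that the sentence says costs are based on this time, not limited to it. The article condenses a fuller plan, which could itemise the programme costs. It also cites the Dutch guidelines and counts intervention costs under the societal perspective. Further, the cost sentence refers to health care professionals, whereas the trainees are called home care professionals elsewhere. The interventionists' profession is not stated, so if they are health care professionals their time could fit the wording.

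This stands in part: deliberate exclusion is not shown. It does not remove the point. The article gives a rule rather than staying silent, treats the trainers as a separate group, and nowhere says that their time is counted. Newsletter production is not covered on either reading.

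A reader might infer more than the documents support:

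- **That role models and newsletters are left out altogether.** Role-model sessions and newsletter reading are professionals' time and can fall within the basis. Only newsletter production is clearly outside it.
- **That preparation, travel and rooms are omitted.** The article does not describe these as resources of the programme.
- **That the planned sensitivity analyses cannot address the gap.** Varying prices and volumes is given as an example, so the list is open. Varying the listed items would not by itself bring in an unnamed one, but other analyses are not ruled out.

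**Conclusion.** The point holds in a limited form. The stated basis for intervention costs does not name trainer time or newsletter production, and this conflicts with the societal perspective. Applied literally, it understates incremental cost in the intervention arm alone and favours the programme.

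That direction needs only that delivery costs are positive and that controls receive no training. The size is not in the documents. The 12 contact hours per trainer per area rest on the schedule and on separate team meetings in each area. The EUR 14 to 138 per trial client rests on assumed staffing, preparation and prices, excludes newsletter production, and is lower when spread over all clients served.

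A reader might conclude that the cost-effectiveness result will be seriously distorted. The documents do not support that: the bias may be small, and nothing shows that it would change a decision. It concerns the economic evaluation only and does not touch the primary outcome. It is still worth correcting, because the bias runs in one direction and the correction is cheap.

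**What to change.** In the section Health care utilisation and costs, extend the rule so that intervention costs comprise:

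- professionals' time on training activities, as now;
- trainer time for delivery and any preparation or travel;
- production of newsletters and materials.

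If an item is to stay out, say so and justify it against the societal perspective. Add trainer hours to the project logbook, which is already kept throughout implementation. Table 3 marks its specific data as still to be specified, so this fits. Contact hours for sessions already held can be rebuilt from the schedule.

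Name the valuation source for intervention costs, spread the costs over all clients served by the trained professionals, and report the training-time-only version as a sensitivity analysis.

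The cost is a short time log, a few sentences of text and a slightly less favourable ICER. Design, sample size and the effect evaluation are unchanged.
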